## End of Study Definition

A participant is considered to have completed the study if he or she has completed all phases of the study including the last visit or the last scheduled procedure shown in the Schedule of Events (Section 7.11).

## Study Discontinuation and Closure

This study may be temporarily suspended or prematurely terminated if there is sufficient reasonable cause. Written notification that documents the reason for study suspension or termination will be provided by the suspending or terminating party to OHSU Coordinating Center, local IRB, and other regulatory authority (if required). If the study is prematurely terminated or suspended, the Investigator must promptly inform the IRB and provide the reason(s) for the termination or suspension. The OHSU Coordinating Center will notify sub-site(s) of any study suspension or discontinuation.

Reasons for terminating the study may include the following:

• Unfavorable assessment of risk/benefit ratio

• Incidence or severity of adverse events, in this or other studies, that indicates a

potential health hazard to participants

• Demonstration of lack of efficacy that warrants stopping

• Data that are not sufficiently complete and/or evaluable

• Investigator not adhering to the study protocol or applicable regulatory guidelines in conducting the study

• Participant enrollment is unsatisfactory

• Submission of knowingly false information from the study site to OHSU Coordinating Center or regulatory authority

• Upon instruction by local or other regulatory or oversight authority.

The study may resume once concerns about safety, protocol compliance, and/or data quality are addressed as applicable and requirements of the OHSU Coordinating Center, funder, IRB and/or other applicable regulatory authority are satisfied.

# STUDY POPULATION

## Participant Inclusion Criteria

To be eligible to participate in this study, an individual must meet all of the following criteria:

1. Participant scheduled for open pancreaticoduodenectomy or distal pancreatectomy for any diagnosis
2. Participant ≥ 18 years of age
3. Ability to understand nature and individual consequences of clinical trial
4. Written informed consent from participant or legally authorized representative.
5. For participants of childbearing potential, a negative pregnancy test and adequate contraception until 14 days after trial intervention
6. Participant needs to have an operative drain (any closed suction drain) after the procedure.
7. Participants that do not require arterial reconstruction
8. Participants that require minor portal venous recounstructions including patch venoplasty

## Participant Exclusion Criteria

An individual who meets any of the following criteria will be excluded from participation in this study:

1. Patients with previous history of adverse reaction to contraste dye, ICG or components of the dye
2. Prior pancreatectomy
3. Known diagnosis of hepatic insufficiency, hepatitis, liver fibrosis or cirrhosis, or chronic pancreatitis
4. Because this study focuses on hypoperfusion, patients will be excluded if in postoperative day 3-5 had any of the following: persistent SBP <90 mmHg unresponsive to 1L crystalloid, unexpected ICU transfer, blood transfusion of >2 units intraoperatively or 1 postoperatively, vasopressor treatment or ACLS protocol initiation
5. Organ failure, anuria or NSQIP-identified complication will be reviewed by PI and attending surgeon and excluded
6. Patients that require arterial reconstruction as part of their procedures

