| **Secondary Objectives** | Evaluate the grade of leak via ISGPS classification and ICG metrics  Determine feasibility of intraoperative measurement of pancreatic perfusion using ICG and the SpyElite platform via a survey to be completed by OR staff.  Evaluate logistics of intraoperative perfusion measurement for staff and operating room using a survey. |
| **Primary Endpoint** | Incidence of biochemical leak or fistula after pancreatectomy defined by definitions of the ISGPS criteria |
|  | |
| **Key Inclusion Criteria** | Patients undergoing open pancreaticoduodenectomy or distal pancreatectomy for any diagnosis will be evaluated for inclusion. |
| **Key Exclusion Criteria** | Development of intra- or post-operative occurrences known to be associated with postoperative pancreatic fistula including hemorrhage, intraoperative blood transfusion, sustained postoperative hypotension requiring vasopressor support, unexpected ICU transfer, initiation of ACLS protocols will be excluded.  Patients with adverse reactions or allergies to indocyanine green will be excluded. History of prior pancreatectomy, prior severe pancreatitis, history of chronic pancreatitits, visceral vascular abnormalities, severe atherosclerosis, planned vascular reconstruction, hepatic insufficiency, liver fibrosis or cirrhosis will be excluded. |
| **Number of Participants** | *n* = 50 patients; anticipate screening *n =* 75 individuals. |
| **Duration of Therapy** | One 5.0 mg IV dose of indocyanine green, intraoperatively, with repeat intraoperative dosing up to maximum 2mg/kg |
| **Duration of Follow Up** | Thirty (30) days. |
|  | |
| **Description of Study Intervention** | Study participants will undergo one intraoperative measurement of pancreatic remnant perfusion. This involves intravenous administration of indocyanine green dye during their operation followed by immediate near-infrared perfusion measurement using the Stryker SpyElite camera, targeted at the organ of interest prior to drug administration. The intervention is expected to take five minutes total. |
|  | |

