| **Statistical Analyses** | Chi-square test will be used to evaluate the association between leaks and perfusion. Logistic regression analysis will be further utilized to evaluate covariates influencing the presence/absence of leaks, with specific attention to the predictive value of percent maximum perfusion metrics and time to maximum metrics at the set timepoints in the protocol. With leaks of any severity occurring in a minimum 20% of pancreatectomies based on extensive published data. Our projected sample size of 50 will achieve 80% power to detect at least 25% difference in leaks rate between two group assuming 20% leak rate for normal ICG perfusion group.  We plan to enroll patients on a rolling basis. With a liberal estimated exclusion of 30% due to the multiple and complex postoperative factors known to be associated with leak (hemorrhage, sustained hypotension, vasopressor requirements included in “Exclusion Criteria”) we anticipate screening 75 patients and enrolling 50. The overall study will be paused if the following events occur: Life-threatening grade 4 toxicity attributable to protocol therapy that is unmanageable, or unexpected, death suspected to be related to ICG injection, as indicated by statistical stopping rules in this protocol. |

SCHEMATIC OF STUDY DESIGN

[figure not shown]

|  | **Preop visit** | **Surgery and Postoperative Period** | | | | |
| --- | --- | --- | --- | --- | --- | --- |
| **Procedure** |  | **Day 1 (Day of Surgery)** | **Day 4±3**  **(Post-operative Day 3)** | **Day of Discharge** | **Discharge + 7-14 Days (Post-Operative Follow-up)** | **Day 30** |
| Physical exam | x | X | X | X | X |  |
| Vital signs^1^ | x | X | X | X | X |  |
| ECG (if indicated) | x | X |  |  |  |  |
| Routine blood draw^2^  (1 tablespoon) |  | X | X |  |  |  |
| Drain Fluid Analysis for amylase |  |  | X |  |  |  |
| Pregnancy test (if indicated) | x | X |  |  |  |  |
| Review any adverse events |  | X |  |  | X | X |
| Review all other medications |  | X |  |  |  |  |
| ICG |  | X |  |  |  |  |
| Pancreas Resection |  | X |  |  |  |  |

TABLE OF CONTENTS

[TABLE OF CONTENTS 7](#_Toc1924134513)

[LIST OF TABLES 7](#_Toc453567276)

[LIST OF FIGURES 7](#_Toc1478094859)

[LIST OF ABBREVIATIONS 7](#_Toc1089401493)

[0. BACKGROUND INFORMATION AND SCIENTIFIC RATIONALE 9](#_Toc2112760570)

[0.0 Background 9](#_Toc1747993032)

[0.0.0 Overview of study disease(s) 9](#_Toc2072564894)

[0.0.1 Overview study intervention(s) 10](#_Toc2069882099)

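### The synopsis and Section 3.1 item 4 set incompatible intra- and postoperative exclusions, neither contains the other, and the choice can be made once leak status is known

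*Protocol*

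**What the plan says.** **Synopsis, Key Exclusion Criteria.** The row opens with "Development of intra- or post-operative occurrences known to be associated with postoperative pancreatic fistula" and lists "hemorrhage, intraoperative blood transfusion, sustained postoperative hypotension requiring vasopressor support, unexpected ICU transfer" and initiation of ACLS. It gives no unit threshold for transfusion and no day window.

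**Synopsis, Statistical Analyses.** This row names hemorrhage, sustained hypotension and vasopressor requirements as exclusion factors. Here hypotension stands without the vasopressor qualifier.

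**Section 3.1, item 4.** The lead-in is "patients will be excluded if in postoperative day 3-5 had any of the following". The list includes "persistent SBP <90 mmHg unresponsive to 1L crystalloid", unexpected ICU transfer, and "blood transfusion of >2 units intraoperatively or 1 postoperatively, vasopressor treatment or ACLS protocol initiation". Hemorrhage is not named anywhere in 3.1.

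**Section 3.1, item 5.** Organ failure, anuria or an NSQIP-identified complication is reviewed by the PI and attending surgeon and excluded. No window is given.

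**Section 6.3.** Vasopressor need during ICG administration is only a possible exclusion, weighed at final analysis.

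**Section 4.1.** A participant counts as enrolled once the study intervention is performed.

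**Section 4.4.** A newly developed exclusion criterion is a reason for discontinuation. Participants who discontinue after the intervention still count toward the enrolment total.

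**Section 10.2, efficacy evaluable population.** It is defined by the operation, ICG injection and up to 30 days of follow-up. None of the exclusions above is mentioned.

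**The concern.** The protocol itself describes these events as associated with fistula, and they may also bear on perfusion. They therefore sit close to both sides of the primary comparison of leak by perfusion group. If two incompatible rules decide who stays, the study has two possible populations and no stated way to choose between them.

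Timing makes this worse. Apart from intraoperative events that precede imaging, the exclusions are met after ICG has been given and the participant is enrolled. Drain amylase, which is sufficient on its own to diagnose a leak under Section 7.1, is taken around postoperative day 3 or 4. A decision to keep or drop a patient can thus be taken by someone who knows whether the patient leaked. Neither the leak rate nor the association could then be matched to a rule fixed in advance.

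**Working it through.** **Step 1. Set the two rules side by side for single-event patients.** Each patient has the stated event and no other.

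| Patient | Synopsis, Key Exclusion Criteria | Section 3.1 item 4 as worded |
| --- | --- | --- |
| 1 or 2 units intraoperatively | Out (no threshold) | In (needs more than 2) |
| Vasopressor-treated sustained hypotension on postoperative day 1 or 2 only | Out (no window) | In (outside days 3-5) |
| Unexpected ICU transfer or ACLS before postoperative day 3 only | Out | In (outside days 3-5) |
| SBP below 90 mmHg unresponsive to 1 L on day 4, no vasopressors | In (vasopressor support required) | Out |
| 1 unit on day 4, no hemorrhage | In (postoperative transfusion not named) | Out |

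The first three rows go one way and the last two the other. Neither rule is a subset of the other, so applying the stricter one does not resolve the conflict.

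**Step 2. Check item 4 against itself.** The lead-in places every listed event in postoperative days 3-5, yet the list contains "blood transfusion of >2 units intraoperatively or 1 postoperatively". An intraoperative transfusion cannot fall in that window. Either the window does not govern every item, in which case the text does not say which it governs, or that part of the item can never be met.

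**Step 3. Look for a passage that settles it.**
- Item 5 has no window and may catch some early events, but it is a review by the PI and attending surgeon, and the documents do not define the NSQIP complications.
- Section 6.3 covers only vasopressors during ICG administration, and only as a possibility.
- Section 4.4 lets a new exclusion criterion end participation but does not say whether the data already collected are analysed.
- Section 10.2 does not mention these exclusions.

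None of these fixes a threshold, a window or an analysis consequence.

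**Step 4. How sensitive is the primary test?** The inputs are the planning values of Section 10.1: 50 patients in balanced groups (25 v 25) and a 20% leak rate under normal perfusion with a 25-point difference, hence 20% v 45%. Section 10.3 gives a chi-square test at 0.05 and does not mention a continuity correction.

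Expected leaks are 0.20 × 25 = 5 and 0.45 × 25 = 11.25, taken as 11.

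Uncorrected test: z = |p1 − p2| / √[p̄(1 − p̄)(1/n1 + 1/n2)].

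- 5/25 v 11/25: p̄ = 16/50 = 0.320; z = 0.240 / √(0.320 × 0.680 × 0.0800) = 0.240 / 0.1319 = 1.82; **p = 0.069**.
- One leaking patient removed from the normal-perfusion group, 4/24 v 11/25: p̄ = 15/49 = 0.306; z = 0.273 / √(0.306 × 0.694 × 0.0817) = 0.273 / 0.1317 = 2.08; **p = 0.038**.
- One leaking patient removed from the reduced-perfusion group instead, 5/25 v 10/24: z = 0.217 / 0.1317 = 1.65; **p = 0.10**.

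With Yates' continuity correction (|p1 − p2| reduced by ½(1/n1 + 1/n2)), the first two become 0.13 and 0.078. It then takes two leaking patients removed from the normal-perfusion group (3/23 v 11/25) to reach 0.041.

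**Step 5. How many patients does this touch?** The documents do not say. The 30% in Section 10.1 is an allowance for all postoperative exclusions. It is not the share on which the two rules disagree, and it is paired with 75 screened and 50 enrolled (75 × 0.70 = 52.5), so the 50 may already be net of exclusions.

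**The case against.** The strongest defence is that a synopsis is a summary and Section 3.1 governs. On that view the transfusion item carries its own timing, bleeding is handled through transfusion units and item 5, and item 5 with Section 6.3 picks up early events. The synopsis list is also introduced as examples, so it need not be complete.

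Part of this stands. A reader might infer that early hypotension, ICU transfer or ACLS is left uncovered by 3.1. The documents do not support that flatly, because item 5 has no window and Section 6.3 touches vasopressors on the day of surgery. How much they catch cannot be told from the text. A reader might also take the missing hemorrhage item as proof of a different population. That is weaker than it looks: the reference to exclusion criteria in the synopsis's Statistical Analyses row may point to the synopsis's own list. It is a drafting gap to close.

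A reader might further infer that the synopsis is simply the broader rule. It is not: its hypotension criterion is "hemorrhage, intraoperative blood transfusion, sustained postoperative hypotension requiring vasopressor support", so on severity item 4 is the wider one.

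The defence fails on the main point. A summary may omit detail, but here it excludes patients whom the full criterion keeps. No precedence clause is stated, and an open list of examples makes the rule less definite. Nor is this detail that a statistical analysis plan would normally supply, since the protocol states eligibility twice and the statements disagree.

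**Conclusion.** The contradiction is established from the text alone. The synopsis and Section 3.1 item 4 disagree on the transfusion threshold, the definition of hypotension and the event window, in both directions, and item 4 is inconsistent within itself. It should be corrected before outcomes are reviewed.

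The size is unknown. It is tempting to put a number on the patients who would change status, but the protocol gives no event rates and any such figure would be invented. What can be shown is sensitivity: at the planning values, removing one leaking patient moves an uncorrected chi-square p-value from 0.069 to 0.038 or to 0.10, depending on the group; with a continuity correction, crossing 0.05 takes two. This assumes balanced groups and leaks at the planned rates. It illustrates fragility and does not predict the result.

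A reader might also conclude that either rule certainly removes patients from the analysis. The documents do not establish that, because Section 10.2 does not mention these exclusions. That silence adds to the problem: both the rule and its consequence are open, and both can be settled after leak status is known.

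**What to change.** Reconcile the synopsis (Key Exclusion Criteria and Statistical Analyses), Section 3.1 items 4 and 5, Section 6.3 and Section 10.2 into one rule that:

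1. gives one transfusion criterion, stated outside the day 3-5 clause;
2. gives one hypotension and vasopressor definition;
3. gives one event window and says which items it governs;
4. either lists hemorrhage in 3.1 with a definition or removes it from the synopsis;
5. says whether meeting the rule after ICG removes a participant from the efficacy evaluable population;
6. is applied by someone without knowledge of leak status.

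Record units, event dates, and whether each event came before or after imaging, for every participant given ICG. A sensitivity analysis under the other wording is optional. The choice of clinical thresholds and window belongs to the investigators.

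The cost is a short amendment and a few CRF fields. Section 6.1 already requires transfusions to be listed on the CRF. No extra patients or procedures are needed.

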# OBJECTIVES AND ENDPOINTS

## Primary Objective and Endpoint

| **Primary Objective** | **Endpoint** | **Start** | **End** |
| --- | --- | --- | --- |
| To determine if altered measurement results of ICG after pancreatectomy is associated with leak rates. | Incidence of biochemical leak or fistula after pancreatectomy defined by definitions of the ISGPS criteria | Day of surgery | Measurement of drain fluid amylase in postoperative period up until day 30 |
|  | Perfusion status measured by ICG metrics | Day of surgery | Day of surgery |

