## ISGPS DEFINITION AND GRADING OF POSTOPERATIVE PANCREATIC FISTULA

We will grade each patient’s postoperative characteristics via the ISGPS grading system. Bile Leak (previously grade A): increased drain amylase activity > 3 times the upper limit of institutional normal serum amylase activity. Grade B: bile leak criteria plus any of the following: persisting peripancreatic drainage >3 weeks, clinically relevant change in management of POPF, POPF percutaneous or endoscopic specific interventions for collections, angiographic procedures for POPF related bleeding. Grade C: whenever Grade B fistula requires reoperation, has signs of infection related to POPF with organ failure, POPF related organ failure or POPF related death.^28^

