11.3.3 Efficacy evaluable population

The efficacy evaluable population includes all participants enrolled in this study who underwent pancreaticoduodenectomy or distal pancreatectomy, received ICG injection and had up to 30 days of postoperative follow-up for complications. Safety analyses for surgery will use the efficacy population.

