Data collection for 30-day postoperative complications, including rates of fistula formation, will be performed by a trained NSQIP surgical clinical reviewer. Due to the workflow of NSQIP reviewers, a lag period between surgery is anticipated equaling up to 3-months. For the interim efficacy analysis, subject charts may be reviewed for information relevant to the primary endpoint by individuals other than the NSQIP reviewer. Data obtained from the NSQIP reviewer relating to primary or secondary endpoints will be separately reviewed by a member of the study team and any conflicts or discrepancies resolved. Finalized data will be entered into the EDC system and used for final analysis.

- - 1. Future Use of Stored Specimens and Data

With patient’s and IRB approval, tissue samples from the pancreas will be stored within the Oregon Pancreas Tissue Registry IRB00003609. Consent for aforementioned IRB is separate from this study (25055). Collection of blood could also be performed for further studies. These samples are used to better understand pancreatic pathologies and their complications. Consent of tissue storage can be withdrawn at any time by patients.

- - 1. Maintenance of Records

Records and documents pertaining to the conduct of this study, source documents, consent forms, laboratory test results and medication inventory records, must be retained by the Investigator for a period of 2 years following the date a marketing application is approved for the drug for the indication for which it is being investigated; or, if no application is to be filed or if the application is not approved for such indicate, until 2 years after the investigation is discontinued and FDA is notified. It is the responsibility of the sponsor to inform the Investigator when these documents no longer need to be retained.

If the Investigator relocates or for any reason withdraws from the study, the study records must be transferred to an agreed upon designee, such as another institution or another investigator at OHSU. Records must be maintained according to institutional or FDA requirements.

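### Exclusion items 4 and 5 remove enrolled patients for postoperative events that are, or can follow from, the primary outcome; the loss falls mainly on Grade B and C leaks

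*Protocol*

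**What the plan says.** **Exclusions.** In Participant Exclusion Criteria, item 5 reads "Organ failure, anuria or NSQIP-identified complication will be reviewed by PI and attending surgeon and excluded", with no time window. Item 4 says "patients will be excluded if in postoperative day 3-5 had any of the following" and lists persistent hypotension, unexpected ICU transfer, transfusion, vasopressor treatment and ACLS. Its list also contains an intraoperative transfusion threshold. The synopsis excludes intra- and postoperative events because they are associated with fistula. Sample Size Determination allows 30% exclusion for such postoperative factors, going from 75 screened to 50 enrolled.

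**Outcome.** The primary endpoint is "Incidence of biochemical leak or fistula after pancreatectomy defined by definitions of the ISGPS criteria", and its end point in time is "Measurement of drain fluid amylase in postoperative period up until day 30". The NSQIP text under Source Data/Documents (13.1.3) says "Data collection for 30-day postoperative complications, including rates of fistula formation, will be performed by a trained NSQIP surgical clinical reviewer"; after reconciliation, those data feed the final analysis. The ISGPS grading section makes a fistula Grade C when, among other things, it "has signs of infection related to POPF with organ failure, POPF related organ failure or POPF related death". It counts angiographic treatment of leak-related bleeding as Grade B.

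**Who is analysed.** Enrollment Procedures counts a patient as enrolled when the study intervention is given. Participant Discontinuation or Withdrawal lists a newly developed exclusion criterion as a reason to leave the study. The efficacy evaluable population (11.3.3) requires resection, ICG and follow-up, and does not mention items 4 or 5. It adds "Safety analyses for surgery will use the efficacy population".

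**The concern.** An exclusion applied after enrolment is harmless to an association only if it is unrelated to the outcome. Here a fistula found by NSQIP is, on the literal text, both the primary event and a reason for removal. Organ failure caused by a leak is both a grading criterion and a reason for removal. ICU transfer, vasopressors or transfusion on days 3-5 may precede a leak or result from it, and item 4 does not distinguish the two.

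Three things are at stake. The leak rates and their difference shrink. The leak-grade objective loses the grades that it most needs. And the item 5 decision is left to the PI and the attending surgeon without stated criteria or blinding to leak status, so removals may differ between perfusion groups in a way that nobody could later reconstruct.

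**Working it through.** **Inputs.** From Sample Size Determination: N = 50, balanced (25/25), 20% leaks with normal perfusion, a 25-point difference (so 45% with reduced perfusion), stated power 80%. From General Approach: alpha 0.05; two-sided is assumed because sidedness is not given. The share *f* of leaks removed is not in the document and is an assumption, shown as a range.

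**The plan's own figure first.** Pooled two-proportion formula:

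power = Φ{[Δ − 1.96·√(p̄(1−p̄)(1/n₁+1/n₂))] / √(p₁(1−p₁)/n₁ + p₂(1−p₂)/n₂)}

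With p₁ = 0.20, p₂ = 0.45, p̄ = 0.325 and n₁ = n₂ = 25: Φ{(0.25 − 0.2597)/0.1277} = Φ(−0.076) = 47%. One-sided it is 60%. The stated 80% is not reproduced, but that is a separate defect. For this point, 47% is the baseline.

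**Effect of removal.** With no removal the expected leaks are 25 × 0.20 = 5 and 25 × 0.45 = 11.25. If a share *f* of leaks and no non-leaks are removed, the observed rate is p(1−f)/(1−pf). At f = 50%: 0.10/0.90 = 11.1% and 0.225/0.775 = 29.0%, with 22.5 and 19.4 patients left. Power is Φ{(0.179 − 0.240)/0.1226} = 31%.

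| Leaks removed, normal / low perfusion | Observed rates | Difference (points) | Odds ratio | Power, not replaced | Power, replaced to 25/25 |
|---|---|---|---|---|---|
| 0% / 0% | 20.0% v 45.0% | 25.0 | 3.27 | 47% | 47% |
| 25% / 25% | 15.8% v 38.0% | 22.2 | 3.27 | 40% | 42% |
| 50% / 50% | 11.1% v 29.0% | 17.9 | 3.27 | 31% | 35% |
| 75% / 75% | 5.9% v 17.0% | 11.1 | 3.27 | 20% | 23% |
| 25% / 50% | 15.8% v 29.0% | 13.2 | 2.18 | 18% | 20% |

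The odds ratio at baseline is (0.45/0.55)/(0.20/0.80) = 3.27. Equal removal multiplies both odds by the same factor and leaves it unchanged. In the unequal row, the odds are 5.625/13.75 and 3.75/20, and the ratio is 2.18.

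Both power columns are needed because the document is unsettled on replacement. Description of the Study Design aims for 50 patients who complete intervention and follow-up, but the discontinuation section counts patients who leave after ICG towards the enrolment total.

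The rows also assume that no non-leaks are removed. If 25% of leaks and 25% of non-leaks go in each group, the rates stay at 20% v 45%, and power without replacement is 37%.

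**The case against.** The strongest reply is that this is a drafting contradiction rather than a plan to discard leaks. NSQIP endpoint data go to the final analysis, a secondary objective grades leaks, and the efficacy population read alone keeps these patients. Item 4 has a stated rationale: hypotension and transfusion can cause hypoperfusion and so confound the comparison. Surgeons are blinded to ICG results, which limits the attending surgeon's scope for removing patients according to perfusion.

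Much of this stands, and it rules out several stronger readings that a reader might infer:

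- *That the analysis is run with all leaks deleted.* A biochemical leak is defined by drain amylase alone. Without clinical consequences it triggers nothing in item 4, and it is lost under item 5 only if NSQIP records it.
- *That the exclusions take power from 80% to 31% or 20%.* The fall from 80% to 47% has nothing to do with them.
- *That the odds ratio is necessarily biased.* It is not under equal removal.
- *That 30% of leaks are to be removed.* The 30% refers to patients.
- *That surgical safety is certainly analysed without its complications.* This follows only if the exclusions carry into the efficacy population, on which the sections disagree.
- *That item 5 is decided once the outcome is known, or that item 4 events always follow the amylase sample.* Item 5 gives no timing, and the sampling window differs between Laboratory Procedures (day 3 or 4±4) and the Schedule of Events (Day 4±3).

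What the reply does not remove is the text itself. Item 5 has no exemption for fistula, no criteria and no blinding to outcome, and the PI's blinding to ICG results when acting as reviewer is not stated. The confounding rationale covers events before a leak, which item 4 does not isolate.

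**Conclusion.** The defect holds as one of selection on the outcome and of conflicting sections. Items 4 and 5, the synopsis, the discontinuation text and the sample size section impose removals after enrolment for events that are, or can result from, the primary outcome. The efficacy population definition does not. Followed as written, the exclusions take out mainly Grade B and C leaks.

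The size depends on an unknown share. Under the protocol's own rates, equal loss of 25% to 75% of leaks reduces the difference from 25 to between 22 and 11 points, and power from 47% to between 40% and 20% (42% to 23% with replacement). A loss of 25% in the normal group and 50% in the low-perfusion group would lower the odds ratio from 3.27 to 2.18; that unequal pattern is an illustration, not something that the document predicts. It must be fixed before analysis, because a null result could not otherwise be told apart from the removal of leaks.

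**What to change.** Amend the protocol as follows:

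1. Limit exclusions to facts known by the time of ICG injection. Delete item 5, and the postoperative events in item 4 and the synopsis, as reasons for removal from analysis.
2. Analyse every resected patient with a valid ICG measurement and outcome data. Bring the synopsis, exclusion criteria, discontinuation section, sample size section and efficacy population definition into line with this.
3. Record the postoperative events, with dates, as outcomes.
4. Pre-specify one sensitivity analysis that omits patients whose hypotension, vasopressor or transfusion event began before the actual date of the drain amylase sample, classified by someone unaware of ICG result and leak status. The sample date is the workable anchor: with one scheduled drain amylase visit, leak onset is mostly unobserved.
5. Run surgical safety analyses on all treated patients.

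The cost is one amendment; clinical care does not change, and patients otherwise lost from a 50-patient study are kept. The downside is that some leaks with a systemic cause stay in the primary analysis, which the sensitivity analysis addresses.
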